### Randomisation and allocation

Randomisation will be performed by an independent statistician using computer-generated permuted blocks, stratified by prior ovarian intervention (surgery or EST), pregnancy desire, and hormonal treatment. Allocation will be centrally managed through a secure, web-based REDCap platform with concealed randomisation sequence. Site investigators will enrol eligible participants, and group allocation will be automatically assigned by the electronic system.

### Blinding

This is an open-label, non-blinded study. Both physician and patient will be aware of the allocated treatment arm, since blinding is not considered feasible when comparing an interventional procedure (EST) with expectant management according to standard clinical practice. The absence of blinding may influence patient-reported quality of life outcomes; however, it should not affect reproductive or biomarker outcomes, which are objective measures.

### Statistical analysis

Primary analysis will use mixed linear regression models with clustering by patient to compare QoL scores. Secondary analyses will include chi-square for categorical outcomes, repeated measures ANOVA, Kaplan–Meier survival curves for pregnancy rates, and Mann–Whitney U tests for oocyte counts. Analyses will be performed on both intention-to-treat and per-protocol populations. A statistical analysis plan will be finalised prior to database lock.

Secondary outcomes will be analysed as defined in Supplementary Table S1. Continuous outcomes (e.g., VAS, AMH, AFC, cyst diameter, oocyte yield, biomarker levels) will be compared between groups using appropriate parametric or non-parametric tests depending on distribution. Categorical outcomes (e.g., pregnancy rates, adverse events, misdiagnosis) will be compared using *χ*^2^ or Fisher's exact test. Time-to-event outcomes (e.g., time to clinical improvement, time to spontaneous pregnancy) will be analysed using Kaplan–Meier curves and log-rank tests. Effect estimates will be presented with 95% confidence intervals. A detailed Statistical Analysis Plan is provided in the Supplementary Appendix S7.

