### Secondary objectives

To compare pain reduction between groups, measured by the Visual Analogue Scale (VAS) at 6 months and time to improvement.To assess changes in pain-associated biomarkers in serum [cortisol, C-reactive protein (CRP), interleukin-6 (IL-6)] and urine (cortisol, adrenaline, noradrenaline) between baseline and 6 months.To evaluate changes in ovarian reserve markers, including serum Anti-Müllerian Hormone (AMH) and antral follicle count (AFC), between baseline and 6 months.To compare the reduction in cyst size (largest diameter) between baseline and 6 months.To assess reproductive outcomes among women with pregnancy desire during the 24-month follow-up, including spontaneous pregnancies, assisted reproductive technology (ART) pregnancies, number of ART cycles required, and oocyte yield.To compare the number and type of adverse events and complications between groups.To identify the number of misdiagnosed cysts (non-endometriomas) in the sclerotherapy group.To compare treatment-related healthcare costs between groups.To assess endometrioma recurrence or progression during the 24-month follow-up.

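### Continuous secondary outcomes measured at baseline and 6 months are assigned distribution-chosen two-group tests and an unassigned repeated-measures ANOVA, where a pre-specified baseline-adjusted model would be more precise

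*Protocol article*

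**What the plan says.** The Statistical analysis section of the protocol article covers these outcomes in two paragraphs.

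- The first gives the primary outcome a model: "Primary analysis will use mixed linear regression models with clustering by patient to compare QoL scores". For the rest it says: "Secondary analyses will include chi-square for categorical outcomes, repeated measures ANOVA", followed by Kaplan–Meier curves for pregnancy and Mann–Whitney tests for oocyte counts. Repeated-measures ANOVA is not tied to any outcome.
- The second names the outcomes concerned, "Continuous outcomes (e.g., VAS, AMH, AFC, cyst diameter, oocyte yield, biomarker levels", and says that they "will be compared between groups using appropriate parametric or non-parametric tests depending on distribution". It adds: "Effect estimates will be presented with 95% confidence intervals".

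Neither paragraph names a baseline value or a stratification factor as a covariate for these outcomes. Both kinds of information will exist. Under Secondary objectives, the ovarian reserve aim is "To evaluate changes in ovarian reserve markers, including serum Anti-Müllerian Hormone (AMH) and antral follicle count (AFC), between baseline and 6 months", and the biomarker and cyst-size aims are framed as change or reduction over the same interval. VAS is the exception: it is labelled pain reduction but specified as the score at 6 months. Under Randomisation and allocation, three factors are stratified: prior ovarian intervention, pregnancy desire and hormonal treatment.

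Detail is deferred: "Secondary outcomes will be analysed as defined in Supplementary Table S1", and "A detailed Statistical Analysis Plan is provided in the Supplementary Appendix S7". Neither supplement was available for this review.

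**The concern.** For an outcome measured before and after randomised treatment, a model that conditions on the baseline value is at least as precise, in large samples, as comparing either 6-month values or changes. The article uses a regression model for the primary outcome but falls back on two-group tests for the secondary ones. Ignoring stratification factors that predict the outcome costs some further precision.

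The selection rule is a second weakness. If the observed distribution decides between a parametric and a rank test, and no criterion or default is stated, the method for each outcome is open until its data have been seen. In an open-label trial that freedom is better removed. An unassigned repeated-measures ANOVA adds another candidate.

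The outcome where this matters most is ovarian reserve. The Discussion treats its assessment as particularly relevant and suggests that sclerotherapy may be attractive if it spares the reserve. An AMH interval that is wider than necessary is easily misread as showing no harm.

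**Working it through.** **The plan's own figure.** The Sample size section states no SD, correlation, effect size or power for any continuous secondary outcome. Its only related figure is 144 per group for the primary endpoint, from 0.5525 versus 0.715, two-sided α 0.05, power 0.80, the arcsine method and 5% loss.

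- h = 2·asin(√0.715) − 2·asin(√0.5525) = 0.339
- n = 2·((1.960 + 0.842)/h)² = 136.4
- 136.4/0.95 = 143.5, so 144 per group

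The figure reproduces, and this point does not affect it. It supplies the evaluable number used below: 144 × 0.95 = 136.8, taken as 137 per arm.

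**Variance of the treatment effect.** Let r be the correlation between baseline and 6-month values, with equal variances at both times. Relative to a comparison of 6-month values alone:

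- 6-month values only: 1
- change from baseline: 2(1 − r)
- ANCOVA on baseline: 1 − r²

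With two time points, the group-by-time test of a repeated-measures ANOVA is the same as the change-score test, so it belongs in the second line. The ratios to ANCOVA are therefore 1/(1 − r²) for 6-month values only and 2(1 − r)/(1 − r²) = 2/(1 + r) for change. Interval width scales with the square root. All values of r are assumed.

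| r | 6-month only / ANCOVA: variance (CI width) | change / ANCOVA: variance (CI width) |
|---|---|---|
| 0.3 | 1.10 (1.05) | 1.54 (1.24) |
| 0.5 | 1.33 (1.15) | 1.33 (1.15) |
| 0.7 | 1.96 (1.40) | 1.18 (1.08) |
| 0.8 | 2.78 (1.67) | 1.11 (1.05) |

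**What this means with 137 per arm.** The difference detectable at 80% power is (1.960 + 0.842)·√(2v/137) in SD units, where v is the relative variance above. The power columns assume a true effect of 0.3 SD, which is also not in the article.

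| r | Detectable difference: 6-month only / change / ANCOVA | Power at 0.3 SD: 6-month only / change / ANCOVA |
|---|---|---|
| 0.3 | 0.338 / 0.401 / 0.323 | 70% / 56% / 74% |
| 0.5 | 0.338 / 0.338 / 0.293 | 70% / 70% / 82% |
| 0.7 | 0.338 / 0.262 / 0.242 | 70% / 89% / 94% |

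A simulation on normal data (2000 runs per correlation, 137 per arm, 0.3 SD) agrees. Power for the t-test on 6-month values, Mann–Whitney on 6-month values, change score and ANCOVA was 70/68/62/77% at r = 0.4, 70/66/79/87% at r = 0.6 and 70/68/98/98% at r = 0.8.

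**Which comparator applies.** AMH, AFC, cyst size and biomarkers are defined as change, so the 2/(1 + r) column is the relevant one. The larger 6-month-only loss fits VAS alone, and only if its wording is taken literally.

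**The case against.** The strongest reply is that the article is a summary. Per-outcome tests, transformations and covariates are commonly left to a table of outcomes and an analysis plan, and the article points to both. That would answer a complaint about missing detail. It does not fully answer this one, because the article states a method. If the supplements already specify a baseline-adjusted model, the article's sentence should be brought into line with them.

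A reader might infer several stronger points that the text does not support.

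- *That baseline values are thrown away.* Four of the five outcome types are defined as change or reduction, and repeated-measures ANOVA uses baseline too. Baseline is used inefficiently. Only the VAS wording could leave it out.
- *That women with incomplete data are dropped.* No complete-case rule is stated. Only baseline and 6 months are named for most of these outcomes, and an ANCOVA would also lose a woman without a 6-month value. The 10% loss in the Sample size section belongs to the fertility substudy; the main trial assumes 5%.
- *That a rank test cannot deliver the promised estimates and intervals.* A Hodges–Lehmann shift with a 95% CI is a standard companion to Mann–Whitney. A rank test does not by itself give a mean difference or ratio, but the promise can be kept.
- *That the two paragraphs contradict each other on repeated-measures ANOVA.* The first lists families of methods, and the second can be read as including that one. The fault is that it is unassigned.

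It also stands that two-group and change-score tests are valid under randomisation, and that at high correlation the gain over change scores is small.

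**Conclusion.** The point holds as one of efficiency and pre-specification; the stated tests are not invalid. The article commits continuous secondary outcomes with a baseline value to tests chosen by distribution, alongside an unassigned repeated-measures ANOVA, where a model using baseline and strata would do better with the same data.

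Under assumed correlations of 0.5 and 0.7, the cost for outcomes analysed as change is 1.33 and 1.18 times the ANCOVA variance, or intervals about 15% and 8% wider. For VAS read as a 6-month score it is 1.33 and 1.96 times, or about 15% and 40% wider. The 40% figure should not be applied to AMH, AFC, cyst size or biomarkers. These sizes rest on the assumed correlations, equal variances at the two visits and approximate normality, after transformation where needed. Any gain from the stratification factors is additional and cannot be quantified from the article. The sample size is unaffected, and oocyte yield, which has no baseline value, is outside the point.

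**What to change.** For VAS, AMH, AFC, cyst diameter and the biomarkers, replace the distribution-based rule and repeated-measures ANOVA with one pre-specified model: ANCOVA of the 6-month value on arm, baseline value and the three stratification factors, reporting the adjusted difference with its 95% CI. The primary outcome's mixed model may be used instead, provided that it takes baseline as a covariate or constrains the arms to a common baseline mean; an unconstrained group-by-time model with two visits only reproduces the change-score comparison.

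Log-transform AMH and the skewed biomarkers, at baseline as well as at 6 months, and report geometric mean ratios with 95% CIs. Fix in advance which biomarkers this covers. Keep rank tests as a sensitivity analysis. State that the VAS analysis uses the baseline score.

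Oocyte yield needs its own line: the first paragraph fixes Mann–Whitney and the second leaves the test to the distribution.

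The cost is wording in the Statistical analysis section, with Supplementary Table S1 and Appendix S7 made to agree, before outcome data are examined. Baseline values are already implied by the objectives and the strata are recorded at randomisation, so no new data or participants are needed.

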**Methods and analysis:**

ESCOMA is a prospective, multicentre, randomised controlled trial comparing ultrasound-guided ethanol sclerotherapy with expectant management. A total of 288 women with ovarian endometriomas will be randomised in a 1:1 ratio. The primary outcome is change in quality of life at 6 months, assessed using the Endometriosis Health Profile-5 (EHP-5). Secondary outcomes include pain reduction, changes in pain-related biomarkers, ovarian reserve markers, cyst size reduction, reproductive outcomes, adverse events and complications, diagnostic accuracy, and healthcare costs. Analyses will be performed according to both intention-to-treat and per-protocol principles.

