#### Procedure

Analgesic treatment is administered before the procedure, consisting of ibuprofen 1 h before and diazepam ½ hour before. On the day of the puncture, the patient must not present purulent leucorrhoea or genital bleeding.A single puncture is performed, preferably via the vaginal route, although an abdominal approach may be used if required by the patient's condition or by the cyst's characteristics, for example in virginal patients or when marked vascularization is observed along the puncture pathway.The abdominal wall or vaginal canal is disinfected with a povidone–iodine solution.A sterile 17-gauge needle (BD Medical Franklin Lakes, NJ, Becton, Dickinson and Company) is used. Under ultrasound guidance, the needle is advanced into the centre of the cyst and connected, through an extension tube and a three-way stopcock, to a vacuum aspiration system.Aspiration of the endometrioma contents may require dilution with saline solution (SS) when the fluid is thick. The aspirated fluid is measured using a syringe or an adapted measurement system.After nearly complete aspiration, several washes with Saline solution (SS) are performed until clear fluid is obtained.A volume of 100% ethanol equivalent to two-thirds of the aspirated volume is then instilled into the cyst, without exceeding 100 mL.The ethanol is left in place for 15 min without moving the needle, which remains inside the cyst.Subsequently, the cyst is emptied and washed twice with SS, using the same volume as the instilled ethanol.The aspirated fluid is sent to the pathology department for cytological examination to confirm the absence of atypical cells.The 100% ethanol solution used at all participating centres will be identical. The product will be supplied by *Farmacia Carreras*, the authorized provider for hospitals throughout Spain, ensuring consistency and avoiding potential bias related to variations in preparation.

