#### Expectant management group

Participants will continue the treatment they were receiving before study inclusion, or no treatment if none was previously prescribed. During follow-up, medical treatment may be initiated or modified according to clinical circumstances, patient preference, and usual clinical practice. Recommendations are provided to investigators to promote consistency in the management of the expectant-management group across participating centres (Supplementary Appendix 3); however, treatment decisions are not mandated by the study protocol. All concomitant treatments and subsequent changes will be prospectively recorded in the study database. Analgesia and supportive care are permitted in both groups. To minimize potential imbalance in this relevant clinical factor, randomisation will be stratified according to the presence or absence of concomitant hormonal treatment at study inclusion. In addition, the potential effect of hormonal treatment received during follow-up will be accounted for in the statistical analysis, including appropriate adjusted and sensitivity analyses.

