#### Secondary outcomes

Pain reduction (VAS score at 6 months and time to improvement)Changes in pain-associated biomarkers in serum (cortisol, CRP, IL-6) and urine (cortisol, adrenaline, noradrenaline)Ovarian reserve markers (AMH and AFC)Reduction in cyst size (largest diameter)Reproductive outcomes (spontaneous pregnancies, ART pregnancies, number of ART cycles, oocyte yield),Adverse events and complications,Number of misdiagnosed cysts (non-endometrioma)Treatment-related direct medical costs from the healthcare system perspective.Endometrioma recurrence or progression.

Long-term outcomes assessed during follow-up up to 24 months will include endometrioma recurrence or progression, subsequent interventions, and reproductive outcomes among women with pregnancy desire, including spontaneous pregnancies and ART-related outcomes (number of ART cycles, number of oocytes retrieved, and pregnancies achieved through ART).

A detailed description of all secondary outcomes, including definitions, timing and methods of aggregation, is provided in Supplementary Table S1.

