### Sample size

For the primary endpoint (quality of life), the sample size was estimated based on published data reporting an improvement in quality of life—considering patient-reported pain—of approximately 55.25% (range 53%–60%) after conservative management and 71.5% (range 63%–80%) after EST. Assuming a two-sided *α* of 0.05 and a statistical power greater than 0.80, 144 participants per group are required to detect a statistically significant difference between the two proportions (p_1_ = 0.5525 and p_2_ = 0.715). Considering a 5% loss to follow-up, the total sample size will be 288 participants (144 per group). Calculations were performed using the arcsine (arcsin–square-root) approximation for comparison of proportions.

For the fertility substudy (subgroup of women expressing a desire for pregnancy), published data indicate pregnancy rates of approximately 48% after EST (range 37%–55%) and 15% with conservative management. Assuming a two-sided *α* of 0.05 and a *β* of 0.20 (power = 0.80), 33 participants per group are required to detect this difference (p_1_ = 0.48, p_2_ = 0.15). Allowing for a 10% loss to follow-up, the final target will be 37 participants per group, yielding a total of 74 women for the fertility analysis.

These calculations ensure adequate statistical power to detect clinically meaningful differences in both quality of life and reproductive outcomes between treatment groups.

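### Misdiagnosis is listed for a between-group test although cyst contents are verified only in the sclerotherapy arm; it should be a one-arm proportion

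*Protocol article*

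**What the plan says.** The Secondary objectives set a one-arm task: "To identify the number of misdiagnosed cysts (non-endometriomas) in the sclerotherapy group". The neighbouring objectives on adverse events and costs are worded as comparisons; this one is not. The Secondary outcomes list repeats the item without naming an arm.

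The Statistical analysis section treats it differently: "Categorical outcomes (e.g., pregnancy rates, adverse events, misdiagnosis) will be compared using" chi-square or Fisher's exact test. The sentence just before it, on continuous outcomes, says that these "will be compared between groups using appropriate parametric or non-parametric tests depending on distribution", so the natural reading of the paragraph is a comparison of the two arms.

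The only examination of cyst contents in the article is a step of the EST procedure: "The aspirated fluid is sent to the pathology department for cytological examination to confirm the absence of atypical cells". For the control arm the article says "Participants will continue the treatment they were receiving before study inclusion, or no treatment if none was previously prescribed", and describes no puncture, aspiration or pathology.

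The abstract lists among the secondary outcomes "adverse events and complications, diagnostic accuracy, and healthcare costs", and the Discussion uses the same label of accuracy. The inclusion criteria require ultrasound suspicion of endometrioma, and the exclusion criteria remove dermoid, anechoic and high-risk cysts as seen on ultrasound.

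**The concern.** A cyst can be reclassified as something other than an endometrioma only if someone looks at its contents. The article provides for that in one arm. If the test is run as the Statistical analysis section states, the control column holds either zeros that mean nobody looked, or nothing at all. A small p-value would then be an artefact of verification, yet it could be published beside genuine comparisons such as adverse events and be read as an effect of treatment or a failure of randomisation.

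The label of diagnostic accuracy adds to this. Readers commonly take it to mean sensitivity and specificity, which this design cannot supply.

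**Working it through.** **Inputs.** Group size is 144 (Sample size section), used here only as a denominator. The two-sided 5% level is also from that section. The article states no misdiagnosis rate, so 2%, 5% and 10% are assumptions that span a range.

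**The plan's own figure.** With p1 = 0.5525 and p2 = 0.715, the arcsine effect is h = 2·asin(√0.715) − 2·asin(√0.5525) = 0.339, and n = 2·[(1.960 + 0.842)/h]² = 136.4, so 137 per group. Allowing 5% loss gives 137 × 1.05 = 143.9, so 144 (or 137/0.95 = 144.2, so 145). The planned 144 is reproduced closely enough to serve as the denominator.

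**Case A: unverified controls counted as not misdiagnosed.** The table is x/144 (EST) against 0/144 (control). With equal group sizes:

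- Fisher two-sided p = 2·C(144, x)/C(288, x)
- Uncorrected chi-square = 288x/(288 − x), on 1 degree of freedom

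| x in EST | Fisher p | Chi-square p |
|---|---|---|
| 3 | 0.247 | 0.082 |
| 4 | 0.122 | 0.044 |
| 5 | 0.060 | 0.024 |
| 6 | 0.030 | 0.013 |
| 7 | 0.0145 | 0.0074 |

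Fisher crosses 0.05 at six cases and uncorrected chi-square at four. The chance of a spuriously significant result, when the true rate is the same in both arms, is a binomial tail with n = 144:

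| Assumed rate, both arms | Expected cases found in EST | P(X ≥ 6): Fisher p < 0.05 | P(X ≥ 4): chi-square p < 0.05 |
|---|---|---|---|
| 2% | 2.9 | 0.07 | 0.33 |
| 5% | 7.2 | 0.73 | 0.93 |
| 10% | 14.4 | 0.997 | > 0.99 |

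**Case B: unverified controls treated as missing.** There is no control column, so neither test can be computed.

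**What the data do support.** A one-arm proportion with an exact (Clopper–Pearson) 95% CI:

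- 3/144 = 2.1% (0.4% to 6.0%)
- 7/144 = 4.9% (2.0% to 9.8%)
- 14/144 = 9.7% (5.4% to 15.8%)

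These use all 144 allocated women; the actual denominator is the number treated and examined.

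**Diagnostic accuracy.** Sensitivity and specificity need women whose ultrasound does not suggest endometrioma, and the eligibility criteria admit none. The EST arm could give the share of ultrasound-suspected cysts that are something else, that is 1 − positive predictive value (PPV). Even that needs a reference standard for endometrioma, whereas the stated purpose of the cytology is to exclude atypical cells.

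**The case against.** Four points deserve weight.

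- **The governing text may be in the supplement.** The article refers secondary outcomes to Supplementary Table S1 and the detailed plan to Appendix S7, neither of which is shown. The sentence at issue is a list of examples and does not itself contain the words for a between-group comparison. The supplement may well be correct. The article still names misdiagnosis for a two-sample test against its own objective, so the sentence needs correcting either way.
- **The size depends on assumptions.** At a 2% rate Fisher would mislead only about 7% of the time, and the article does not say how unverified controls would be coded. This stands, and is why a range is given. Neither coding yields a valid test.
- **Some control cysts may be verified later.** Subsequent interventions are recorded up to 24 months, so a few controls could yield tissue or fluid. That would be a selected subset and would not rescue the comparison, but it would be wrong to say that no control cyst could ever be verified.
- **The accuracy label is loose wording.** The article nowhere promises sensitivity or specificity, and the objective describes the outcome as a count. This stands, so this part is a matter of terminology.

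Two stronger readings go too far. A reader might infer that no accuracy measure is estimable because one arm lacks fluid. In fact verification in one randomised arm would be enough for 1 − PPV, given a suitable reference standard; sensitivity and specificity are lost because of who is enrolled. A reader might also infer that misdiagnosed women will be dropped from the per-protocol set in the EST arm only, which would disturb the primary comparison. The article says nothing of the kind, and the definition of that set is ordinary analysis-plan content.

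**Conclusion.** The point holds as a minor inconsistency in a secondary outcome. The objective is right, and the Statistical analysis section contradicts it by naming misdiagnosis for a between-group test. Run as written, with controls counted as not misdiagnosed, Fisher's test would be falsely significant with probability about 0.07 to 0.997 across assumed rates of 2% to 10%; with controls missing, it could not be run. These figures rest on 144 women per arm, equal true rates in both arms, complete verification under EST and none under expectant management. Calling the outcome diagnostic accuracy claims more than a one-arm proportion among ultrasound-suspected cysts can show. The primary quality-of-life analysis is not affected.

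**What to change.** 1. In the Statistical analysis section, delete misdiagnosis from the categorical outcomes compared by chi-square or Fisher's exact test.
2. State that it will be reported descriptively as the proportion of EST-treated women with a cyst found not to be an endometrioma, with an exact 95% CI. If it is reported per cyst, allow for clustering within women, because bilateral endometriomas are eligible and a simple binomial interval over cysts would ignore this.
3. In the abstract and the Discussion, replace the term diagnostic accuracy with that proportion. Call it 1 − PPV only if the outcome definition names a reference standard for endometrioma, since the Procedure section gives the cytology a different purpose.
4. Check that Supplementary Table S1 and Appendix S7 agree with the objective.

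The cost is wording only: no change to sample size, data collection or conduct.

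### Kaplan–Meier for spontaneous pregnancy and a between-arm test of oocyte counts do not fit outcomes shaped by assisted reproduction after randomisation

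*Protocol article*

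**What the plan says.** The Statistical analysis section of the protocol article names the methods for the fertility outcomes in three places:

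- For time to event: "Time-to-event outcomes (e.g., time to clinical improvement, time to spontaneous pregnancy) will be analysed using Kaplan–Meier curves and log-rank tests".
- Among the secondary analyses: "Kaplan–Meier survival curves for pregnancy rates, and Mann–Whitney U tests for oocyte counts". Oocyte yield appears again in the list of continuous outcomes to be compared between arms.
- For proportions: "Categorical outcomes (e.g., pregnancy rates, adverse events, misdiagnosis) will be compared using" the chi-square or Fisher's exact test.

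The Secondary objectives define the reproductive outcomes for women with pregnancy desire over 24 months, "including spontaneous pregnancies, assisted reproductive technology (ART) pregnancies, number of ART cycles required, and oocyte yield". The Secondary outcomes section repeats the "ART-related outcomes (number of ART cycles, number of oocytes retrieved, and pregnancies achieved through ART" as long-term outcomes. Spontaneous and ART pregnancy are therefore two outcomes in the same women over the same period.

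Randomisation is "stratified by prior ovarian intervention (surgery or EST), pregnancy desire, and hormonal treatment", so the fertility subgroup is fixed at baseline. The Sample size section sizes it on two pregnancy proportions, 0.48 and 0.15.

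For detail the article points elsewhere: "Secondary outcomes will be analysed as defined in Supplementary Table S1", with a fuller plan in Supplementary Appendix S7. Neither is shown here.

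**The concern.** Two of the named methods fit their outcomes poorly.

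**Spontaneous pregnancy.** A woman who conceives by ART cannot, during that pregnancy, have a first spontaneous conception. Kaplan–Meier has no third state. It must either censor her, as if she could still conceive spontaneously later, or keep her at risk to 24 months. If she is censored, 1−KM answers what would happen if ART pregnancy did not occur. It does not give the proportion who conceive spontaneously, yet a reader will take it as that.

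**Oocyte counts.** Oocytes retrieved exist only for women who undergo a retrieval. Reaching one is a post-randomisation event, and spontaneous conception makes it less likely. The trial itself expects EST to change pregnancy rates. A test on observed counts then compares selected women, and randomisation no longer protects it.

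The Blinding section says of the open-label design that "it should not affect reproductive or biomarker outcomes, which are objective measures". Conception is objective, but the decision to go to ART is taken with allocation known, so ART uptake may differ by arm.

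At stake are the reading of the spontaneous-pregnancy curve and of one between-arm p-value on a fertility measure.

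**Working it through.** **1. The article's own figure.** Inputs from the Sample size section: p1 = 0.48, p2 = 0.15, two-sided alpha 0.05, power 0.80, 10% loss. With unpooled variance:

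n = (1.960 + 0.842)² × (0.48×0.52 + 0.15×0.85) / 0.33² = 27.18.

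With continuity correction: (27.18/4) × (1 + √(1 + 4/(27.18×0.33)))² = 32.96, so 33. Then 33/0.90 = 36.67, so 37 per group and 74 in total. The stated figures reproduce. They rest on a comparison of proportions, so nothing below changes them.

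**2. How far 1−KM overstates.** The documents give no ART rates, so these are assumptions: constant hazards, independent ART, 1−KM for spontaneous pregnancy of 25% at 24 months, and a net ART-pregnancy probability of 10% or 30%. Write S = −ln(1 − 0.25) = 0.2877 and A = −ln(1 − net ART probability). The proportion conceiving spontaneously first is S/(S + A) × (1 − exp(−(S + A))).

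- ART 10%: A = 0.1054; 0.2877/0.3930 × (1 − 0.75×0.90) = 0.732 × 0.325 = 0.238.
- ART 30%: A = 0.3567; 0.2877/0.6444 × (1 − 0.75×0.70) = 0.446 × 0.475 = 0.212.

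Kaplan–Meier shows 25% in both cases, an excess of 1.2 and 3.8 points.

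For a range, take the article's planning rates of 15% and 48% merely as a low and a high level for 1−KM (the article does not say they are spontaneous pregnancies):

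- 15%, S = 0.1625: 0.1625/0.2679 × 0.235 = 14.3% (ART 10%) and 0.1625/0.5192 × 0.405 = 12.7% (ART 30%).
- 48%, S = 0.6539: 0.6539/0.7593 × 0.532 = 45.8% (ART 10%) and 0.6539/1.0106 × 0.636 = 41.2% (ART 30%).

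**3. When less fertile women go to ART sooner.** A large simulation used assumed hazards, with the same underlying fertility in both arms and a 24-month risk without ART of about 0.32. ART was reached by 16% in one arm and 46% in the other, with censoring at ART. Kaplan–Meier gave 0.33 and 0.35; the observed cumulative incidence was 0.31 and 0.27. Kaplan–Meier again exceeded the observed proportion, but the false contrast between arms was only about 2 points.

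**4. The log-rank test.** Assumptions: 37 per arm, equal spontaneous hazard of 0.02 per month, and ART hazards by arm of 0.02/0.02, 0.01/0.04 or 0.005/0.06 per month. Each setting had 4,000 simulated trials.

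- Censoring at ART: rejection 4.7–4.8% with independent ART, and 5.5–6.0% when less fertile women go to ART sooner.
- Keeping ART women at risk to 24 months: 4.7–5.8% with equal ART uptake, and 7.9–17.8% with unequal uptake. This test targets a different quantity, one that responds to ART uptake.

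The handling of ART therefore matters, and the method's name does not settle it.

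**5. Oocyte counts.** Assumptions: no effect of EST on yield (mean 7.8 in all women of each arm), yield rising with underlying fertility, and women not pregnant by month 12 going to ART.

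- Spontaneous-pregnancy hazard ratio about 2 for EST: mean among women reaching ART 6.7 against 7.15.
- Hazard ratio about 3: 6.3 against 7.15.
- No effect on pregnancy: 7.15 against 7.14.

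Selection alone produces an apparent deficit of about 0.5 to 0.8 oocytes for EST.

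**The case against.** The article nowhere says that ART pregnancies are censored, that ART is treated as uninformative, or that oocytes are tested only in women who reach ART. Censoring rules and analysis sets are what a condensed article leaves to Supplementary Table S1 and Appendix S7. This stands: both readings are inferences from the named methods. What remains is that the article itself names those methods, and neither fits its outcome without a further rule.

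A reader might also infer that the planned contrast between arms is biased by ART uptake. The documents and the calculation do not support that. In step 2 the spontaneous hazard does not depend on ART, so two arms with 10% and 30% ART would both show 25% on Kaplan–Meier, correctly no difference. The gap of 23.8% against 21.2% in cumulative incidence would come from ART uptake alone. The two methods answer different questions. The log-rank test censored at ART pregnancy is a valid comparison of cause-specific hazards if censoring is non-informative.

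A further tempting reading is that the fertility analyses as a whole are not randomised comparisons, or that the substudy's power fails. Neither follows. Pregnancy desire is a baseline stratum, and the chi-square or Fisher comparison of proportions within it keeps randomisation and matches the sizing. Time to spontaneous pregnancy is mentioned only as an example of a time-to-event outcome, not as the leading fertility result.

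**Conclusion.** The point holds in limited form. If ART pregnancies are censored, 1−KM overstates the proportion conceiving spontaneously: by 1.2 to 3.8 points at an assumed 25%, and by 0.7 to 6.8 points over the wider assumed range. The error lies in reading the curve as a probability of spontaneous pregnancy, not in the log-rank test.

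A between-arm test on observed oocyte counts compares groups selected after randomisation. In the illustration this cost EST about 0.5 to 0.8 oocytes with no true effect on yield. The size and direction depend on the assumed link between fertility, conception and ART, on which the documents give no data.

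Pregnancy proportions within the pregnancy-desire stratum and the figure of 37 per group stand. These are secondary outcomes, and the primary quality-of-life conclusion is not affected.

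**What to change.** In the analysis plan, and in the article's wording where possible:

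- Show spontaneous pregnancy as cumulative incidence (Aalen–Johansen) with ART pregnancy as a competing event. Label the log-rank test as cause-specific. Read the two together, because a gap in cumulative incidence can come from ART uptake alone.
- Report oocyte yield and number of ART cycles descriptively among ART users, with the number reaching ART in each arm, and with no between-arm p-value read as a treatment effect.
- Make the proportion with any pregnancy (spontaneous or ART) by 24 months, among all women randomised in the pregnancy-desire stratum, the lead fertility comparison. This fits the two-proportion sizing. The article does not say which kind of pregnancy the 48% and 15% count, so the sponsor should confirm that they mean any pregnancy.

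If Table S1 or Appendix S7 already sets these rules, aligning the article's wording is enough. The cost is a few sentences and standard software, with no extra data or participants. The downside is that the oocyte comparison loses its p-value.
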